## Abstract

**Background:**

Diabetic limb ulcers are highly prevalent and contribute to a significant increase in cost for the treatment of these patients in health services. However, healing of these wounds is a major health problem and may even lead to amputation. The primary aim of the current study is to evaluate the efficacy of hyperbaric oxygen therapy (HBOT) in facilitating the healing of diabetic foot ulcers, in addition to secondarily evaluating whether it reduces the number of amputations and improves the quality of life in these patients.

**Methods:**

A non-blind randomized clinical study will be conducted in the city of Imperatriz, Maranhão state, Brazil, from 2019 to 2020, in diabetic patients with chronic foot ulcers (classified as Wagner grades 2, 3 and 4, persisting for more than 1 month). The outpatient follow-up for diabetic foot patients will be done at the Unified Health System, with a sample size of 120 patients (the randomization allocation will be 1:1, being 60 patients for each arm). Half of the patients will receive standard treatment, i.e. dressings, debridement, antibiotics and load relief, along with HBOT (HBOT group), and the other half will receive only standard treatment (control group). The patients of the HBOT group will be evaluated upon admission, after 10, 20, 30 and 35 HBOT sessions, and after 6 months and 1 year. The patients of the control group will also be evaluated at equivalent periods (upon admission, after 2, 4, 6 and 7 weeks, 6 months and 1 year). The SF-36 quality of life questionnaire will be filled upon admission and after 3 months of follow-up in both groups. The primary and secondary endpoints will be assessed with 1 year of follow-up.

**Discussion:**

Diabetic foot ulcers are a highly prevalent complication of diabetes with serious consequences. A study to assess the efficacy of HBOT in healing the ulcers and reducing the rate of amputations in diabetic patients is justified, which will eventually aid in the development of guidelines for treating these ulcers.

**Trial registration:**

Registration number RBR-7bd3xy. Registered on 17 July 2019—Retrospectively registered.

## Background

Globally, more than 400 million adults suffer from diabetes, and the treatment of diabetic foot ulcers is considered as an important public health issue [1]. According to the Ministry of Health of Brazil, the number of diabetic patients in Brazil increased by 61.8% between 2006 and 2016, and the prevalence increased from 5.5 to 8.9%, with more prevalence in women (9.9%) than in men (7.8%). Approximately one in every twenty diabetic patients develops foot ulcers in the first year, and approximately 10% of the patients with ulcers evolve to amputation in this period [2, 3].

Unhealed and infected wounds in diabetic foot cause damage in both tissues and bones, which leads to amputations in 85% of these individuals, and approximately 60% mortality has been reported after amputation during 5 years of follow-up [4–6].

Chronic changes that occur in the feet of diabetic patients, such as peripheral arterial disease, neuropathy with loss of protective sensitivity, deformities and decreased mobility of the feet, are the main challenges in the prevention and treatment of diabetic foot ulcers [7, 8]. The treatment of diabetes and diabetic foot ulcers requires multiple approaches, which involve optimization of glycaemic control, wound care, treatment of infections, load relief and revascularization in ischemic cases [2, 9]. Unfortunately, even with optimal care, the rate of complete healing of the wounds stays approximately 60% per year [2, 10]. Hyperbaric oxygen therapy (HBOT) has been used as an adjuvant therapy for patients with refractory ulcers [11, 12].

Normal wound healing occurs through the ordered and overlapping stages of haemostasis, inflammation, proliferation and tissue remodelling, involving complex molecular and cellular interactions within the wound microenvironment [13]. Regardless of the aetiology of the wound, an adequate condition of the vasculature, including both macrocirculation and microcirculation, is critical for healing. Insufficient perfusion impairs angiogenesis, collagen deposition and epithelialization and may lead to sustained inflammation [14].

Among the advanced therapeutic interventions for wounds, HBOT has the unique ability to improve tissue hypoxia, reduce pathological inflammation and mitigate ischemia-reperfusion injury [15].

Evidence on the effectiveness of HBOT in healing diabetic foot ulcers is variable. Some researchers have reported greater effectiveness when HBOT is compared to sham treatment or placebo [2, 16–19], but others found no differences [7, 20]. HBOT has also been reported to promote the resolution of infection and reduce the likelihood of amputation by some authors [17], but others have shown no benefit [7, 21].

A systematic review of randomized clinical trial data recently published by the Cochrane Collaboration [22] reported a significant improvement in short-term (6 weeks) wound healing, but no statistically significant difference was found in wound healing rates for long-term amputation and major or minor amputation favouring HBOT, thus, suggesting the need for further randomized studies to clarify these doubts.

### Objectives

#### Primary objective

The primary objective is to assess whether HBOT along with the standard treatment of chronic diabetic foot ulcers is more effective in wound healing than the standard treatment alone.

#### Secondary objective

The secondary objective is to assess whether HBOT, along with the standard treatment of chronic diabetic foot ulcers, reduces the number of major (transtibial and transfemoral) and minor amputations (toes and forefoot) and improves the quality of life of these patients, as compared to the standard treatment alone.

### Hypothesis

Adding adjunctive treatment of HBOT to the standard treatment of diabetic foot ulcers, i.e. dressings, debridement, antibiotics and load relief, can improve wound healing and reduce major amputations, improving the quality of life of these patients.

## Methodology

### Study design

This is a parallel, two-arm, non-blinded, randomized controlled trial in the single centre.

### Study site

The study will be conducted in the city of Imperatriz, Maranhão, in diabetic patients with chronic foot ulcers (classified as grades 2, 3 and 4 of Wagner [23] and persisting for more than 1 month). The outpatient follow-up for diabetic foot patients will be done at the SUS (Unified Health System - a public health service for the entire Brazilian population), with HBOT sessions being held in the CicatrizAR Clinic.

### Sample and study period

The sample will consist of diabetic patients with chronic foot ulcers treated with standard methods, i.e. dressings, debridement, antibiotics and load relief (control group), and to the other group will be added HBOT (HBOT group). The study will be conducted from 2019 to 2020.

The sample size has been calculated based on the formula for comparing two independent groups according to qualitative variables [24], with 95% confidence interval and 80% power. A wound healing rate of 90% was considered achievable for the case group at 1 year, which we expected to be at least 20% higher than in the control group (absolute difference, i.e. no more than a wound healing rate of 70% was expected in the control group). Thus, the total sample size was estimated as 60 patients per group (120 in total).

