### Trial status

Registration number RBR-7bd3xy. Registered 17 July 2019. The first recruitment was held on 4 July 2019 and the last recruitment is foreseen on 31 August 2020.

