### Interventions

The patients of the HBOT group will be evaluated upon admission, after 10, 20, 30 and 35 HBOT sessions and after 6 months and 1 year, and the control group will also be assessed at equivalent periods (upon admission, after 2, 4, 6 and 7 weeks, 6 months and 1 year) to clinically evaluate the ulcers and perform specific measures using the software ImageJ, developed at the National Institutes of Health (NIH, Bethesda, Maryland). HBOT sessions will be held 1 week after randomization. The sessions will be supervised by doctors trained in hyperbaric medicine by the Brazilian Society of Hyperbaric Medicine (SBMH). The HBOT sessions will be conducted 5 days a week, being carried out with patients in a multiplace chamber at 2.5 atm absolute (ATA) and 100% O_2_, with 10 min for compression and decompression, effective sessions of 90 min, with intervals of 5 min for each 30 min of treatment. The dressings will be done in both groups with Exufiber foam Ag® (*Molnlycke*, Gotemburgo, Suécia) or Mepilex® (*Molnlycke*, Gotemburgo, Suécia), which will be chosen according to the characteristics of wounds, with silver dressings for the infected injuries and a foam with polyurethane protective layer for wounds in which granulation tissue has formed. Secondary dressings will be changed daily and the primary dressings (coverings—Exufiber foam Ag or Mepilex) will be changed every 3–5 days, as needed and in both groups. The progression of the wounds and specific treatment, such as appropriate bandage, antibiotic therapy or need of some surgical intervention, will be evaluated on a weekly basis. In both groups, a vascular surgeon will monitor the patients, and who will assess the need for surgical procedures (debridement and amputations), in addition to appropriate antibiotic therapy for each case. With regard to load relief, patients in both groups will wear orthopaedic Baruk shoes.

The SF-36 quality of life questionnaire will be filled upon admission and after 3 months of follow-up in both the groups. Laboratory examinations, such as a haemogram, erythrocyte sedimentation rate, levels of C-reactive protein, creatinine, fasting blood glucose and glycosylated haemoglobin will also be estimated only on admission.

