### Primary outcome

Wound healing will be assessed by evaluating the diameter of the lesions by specific software and periods, as described in the interventions. The wound healing will be achieved when there is no more skin lesion on the skin and the primary endpoint will be a binary result. The assessor of the primary outcome will be blinded.

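### The stated study period of 2019 to 2020 does not fit recruitment to 31 August 2020 and a primary endpoint read at 1 year

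*Protocol article*

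**What the plan says.** The protocol article gives four kinds of timing information.

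- **Study period.** The section on sample and study period states "The study will be conducted from 2019 to 2020". The abstract's Methods paragraph places the clinical study "in the city of Imperatriz, Maranhão state, Brazil, from 2019 to 2020".
- **Recruitment.** Trial status reports "The first recruitment was held on 4 July 2019" and adds that "the last recruitment is foreseen on 31 August 2020".
- **Endpoint time.** The abstract states "The primary and secondary endpoints will be assessed with 1 year of follow-up". The Interventions section schedules HBOT-arm evaluations "after 10, 20, 30 and 35 HBOT sessions and after 6 months and 1 year", with equivalent times for controls.
- **Planning assumption.** The sample size rests on 1-year healing: "A wound healing rate of 90% was considered achievable for the case group at 1 year", against no more than 70% in the control group.

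The Primary outcome section adds that "the primary endpoint will be a binary result". It takes its assessment times from the Interventions section and does not itself name the 1-year visit.

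**The concern.** The recruitment window, the visit schedule and the endpoint time agree with one another. The study period does not agree with them. The article applies that period to the conduct of the whole study, gives recruitment dates separately, and nowhere mentions 2021 or an end of follow-up.

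If someone closed the trial on the stated years, patients recruited in 2020 would have roughly 4 to 12 months of follow-up. They would then either have no 1-year result or be counted alongside patients who do. The Data analysis section plans logistic regression for categorical outcomes, with odds ratios and risk differences. As described, that model makes no allowance for unequal follow-up. A healed/not-healed result pooled over mixed durations would no longer estimate the 1-year difference on which the trial was sized. Time point matters here: the Background's account of a systematic review separates 6-week healing, which improved, from longer-term results, which showed no significant difference.

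**Working it through.** **Inputs from the protocol article.** First recruitment 4 July 2019 and last 31 August 2020 (Trial status); study period 2019 to 2020 (abstract; Sample and study period); endpoint at 1 year (abstract); healing 90% vs 70%, 80% power, 60 per group (Sample and study period).

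**Assumptions not in the article.** The year runs from the recruitment date; 2019 to 2020 ends on 31 December 2020 at the latest; the test is two-sided at 5%; accrual is even unless varied below.

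**1. The plan's own sample size.**
- Pooled variance: n = [1.960·√(2·0.8·0.2) + 0.842·√(0.9·0.1 + 0.7·0.3)]² / 0.2² = (1.109 + 0.461)² / 0.04 ≈ 61.6, so 62 per group.
- Unpooled variance: n = (1.960 + 0.842)²·0.30 / 0.04 ≈ 58.9, so 59 per group.
- The stated 60 lies between the two. Power at 60 per group, pooled: Φ[(0.2·√60 − 1.109) / √0.30] = Φ(0.804) = 78.9%.

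The sample size reproduces and is not in dispute.

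**2. Calendar.**
- Recruitment window, both end dates counted: 181 days in 2019 (4 July to 31 December) + 244 days in 2020 (1 January to 31 August) = 425 days.
- Last patient: 1 year after 31 August 2020 is about 31 August 2021, 243 days (about 8 months) after 31 December 2020.
- The same patient has 122 days (17.4 weeks) of follow-up by 31 December 2020, so the 6-month visit also falls outside the stated period.
- Latest enrolment that allows 1 year by 31 December 2020: 31 December 2019.

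**3. Patients affected if follow-up stopped at the end of 2020.**
- Even accrual: 181/425 = 42.6% enrol in 2019. 120 × 0.426 ≈ 51 reach 1 year, and 120 × 0.574 ≈ 69 do not.
- No accrual rate is given, so the share is varied in the table.

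**4. Power if, in addition, only patients with a 1-year visit were analysed.** The formula is the pooled one in step 1, with the reduced number split evenly. For 51 patients: Φ[(0.2·√25.5 − 1.109) / √0.30] = Φ(−0.180) = 42.8%.

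| Share enrolled in 2019 | Reach 1 year by end of 2020 | Do not | Power, 1-year visits only |
|---|---|---|---|
| 30% | 36 | 84 | 32% |
| 42.6% (even accrual) | 51 | 69 | 43% |
| 50% | 60 | 60 | 49% |
| 70% | 84 | 36 | 63% |

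The clash of dates in step 2 needs no accrual assumption. The counts in step 3 need a real stop at the end of 2020 and an assumed accrual pattern. The power figures need both of these and a completers-only analysis.

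**The case against.** The strongest reply is that 2019 to 2020 is a loose label. Those are exactly the calendar years of the recruitment window, while the more specific text commits every patient to a 1-year visit. No section gives a closing date, a database lock or an instruction to stop follow-up on 31 December 2020. On this reading follow-up simply runs into 2021 and no patient loses the endpoint. That may well be the intent, and nothing in the article rules it out. Equally, nothing in the article says it: the years are attached to the study being conducted, not to recruitment.

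A reader might go further and infer that more than half of the patients would lack the primary outcome and that the planned power would be lost. The documents do not support this, for three reasons.

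- It requires follow-up to stop at the end of 2020, which no section orders.
- It requires even or later-weighted accrual. If more than 60 of the 120 enrolled by 31 December 2019, the share falls below half.
- The power figure requires patients without a 1-year visit to be dropped. The Data analysis section specifies intention-to-treat and active search to avoid sample loss, and plans no completers-only analysis. Healing is also assessed at earlier visits, so a patient cut short could still contribute some outcome information.

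Two points stand against the reply. Active search addresses patients who are lost, not a study that closes before the visit is due. And intention-to-treat does not say how a 1-year result would be obtained for a patient followed for 4 months.

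**Conclusion.** The point holds as an internal inconsistency. The stated study period cannot contain the 1-year endpoint for anyone recruited after 31 December 2019, and recruitment is planned for 8 months beyond that date. This follows from the dates alone.

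The consequence is conditional. Only if follow-up closed at the end of 2020 would about 57% of patients lack the 1-year assessment under even accrual, within the range tabulated above. Power near 43% carries the further condition of a completers-only analysis. No loss of the primary outcome is demonstrated. The text still needs correcting, because it leaves open whether the primary endpoint will be observed in everyone, and the stated date, if followed, would defeat it.

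**What to change.** In the abstract and in the section on sample and study period, restate the study period as 4 July 2019 to the last patient's 1-year visit, about 31 August 2021 plus the visit window. State that the between-arm primary analysis is run only after that visit. If 2019 to 2020 was meant as the recruitment period, label it so.

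The cost is a date amendment and follow-up for about 8 months into 2021. The per-patient schedule already requires those visits, so no procedure is added. Whether the registry entry carries the same period cannot be checked from the article.

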### Trial status

Registration number RBR-7bd3xy. Registered 17 July 2019. The first recruitment was held on 4 July 2019 and the last recruitment is foreseen on 31 August 2020.

### Eligibility criteria

The inclusion criteria of the study are adult patients (age > 18 years); stable clinical presentation; diabetes type 1 and 2; Wagner grades 2, 3, and 4 foot ulcers; ulcers persisting for more than 1 month without cure; authorization for the study; and patients of the SUS (Unified Health System).

Exclusion criteria of the study are failure to meet one of the inclusion criteria, patients with macroangiopathy (two distal pulses absent) and patients with contraindications for HBOT, absolute or relative, patients on bleomycin chemotherapy, with chronic obstructive pulmonary disease, previous spontaneous pneumothorax, chronic sinusitis, chronic otitis media, unstable angina, severe congestive heart failure, claustrophobia, severe dementia, depression and history of seizures.

### Data collection

The data collection will be performed in the diabetic foot outpatient clinic of the SUS and in the CicatrizAR clinic, using a standardized questionnaire provided in the Supporting Information, as well as with photographic recording of the ulcers, according to the timeline described in Fig. 1.

**Fig. 1 Fig1:**
[figure not shown]
The schedule of enrolment, interventions and assessments

### Randomization

This is a parallel, two-arm, non-blinded, randomized controlled trial in which an randomization will be performed by the research coordinator, who will carry out by simple 1:1 draw (for each pair of patients, one participant will select the number 1 or 2 in the draw, which will correspond to the group to be allocated, while the second patient will be allocated to the other group.). The randomization will not be done by computer-generated random numbers. Patients will be selected at the SUS diabetic foot clinic, where they regularly monitor the lesions on their feet. They will be evaluated according to the inclusion criteria of our research and, if they meet the criteria, they will be invited to participate in the research. The researchers explain how the study will be carried out and after 1 week, if the patient is interested in participating in the study, the research coordinator collects the signature of the patient’s consent form that found in the support information for this article, as well as performs the randomization of patients to the research groups.

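### Allocation in pairs by a single manual draw, run by the coordinator who also takes consent and with no concealment step, leaves up to half of the allocations foreseeable

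*Protocol article*

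**What the plan says.** The Randomization section of the protocol article describes a manual draw: "for each pair of patients, one participant will select the number 1 or 2 in the draw", "while the second patient will be allocated to the other group". It labels this a simple draw and adds: "The randomization will not be done by computer-generated random numbers".

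The same section says who acts. The "randomization will be performed by the research coordinator". About a week after the researchers have explained the study, "the research coordinator collects the signature of the patient’s consent form" and, in the same step, "as well as performs the randomization of patients to the research groups".

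Study design states: "This is a parallel, two-arm, non-blinded, randomized controlled trial in the single centre". Primary outcome states: "The assessor of the primary outcome will be blinded". Data analysis extends blinding to the researcher who evaluates the final data and to the statistician. No section mentions sealed envelopes, a central service or a third party holding the sequence. None says whether the two members of a pair are both enrolled before the draw.

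**The concern.** One chance event settles two patients. In an unblinded trial at one centre the coordinator sees the result of the draw. If the second member of the pair has not yet consented, the coordinator knows that patient's arm while still taking consent. The order in which patients are brought in, and how strongly they are encouraged, can then depend on the arm that is due, without any intent.

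There is prognostic room for this to matter. Entry covers Wagner grades 2 to 4, a wide range, and requires a stable clinical presentation and no absolute or relative contraindication to HBOT, both of which call for judgement.

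Selection at entry would act directly on the primary comparison of healing. Intention-to-treat keeps patients in the arm assigned, so it preserves any imbalance created at entry. Blinding of the assessor, the data evaluator and the statistician starts only after entry.

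**Working it through.** **Inputs from the protocol article.** Pairs with the second patient in the opposite arm (Randomization); 1:1, 60 per arm, 120 in total (Abstract, Methods); healing of 90% against 70%, 95% confidence, 80% power (Sample and study period).

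**The plan's own figure.** With unpooled variance, n = (0.9×0.1 + 0.7×0.3) × (1.960 + 0.842)² / 0.20² = 0.30 × 7.85 / 0.04 = 58.9, so 59 per arm. The pooled formula gives 62. The stated 60 is reproduced, and its power by the pooled formula is 78.9%. The sample size is not in dispute.

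**Predictability if patients enter one after another.**
- Pairs: 120 / 2 = 60, so 60 of 120 arms (50%) are determined before that patient enters.
- Expected correct guesses: 0.5 × 0.5 + 0.5 × 1 = 0.75.
- If both members are consented before the draw, neither arm can be foreseen, and the share determined before consent is 0.

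**Comparison with other blocking**, for a guesser who sees past allocations (simulated):

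| Scheme | Arms certain | Correct guesses |
|---|---|---|
| Fixed blocks of 2 | 50% | 75% |
| Fixed blocks of 4 | 33% | 71% |
| Random blocks of 4, 6, 8, each size known to the guesser | 25% | 68% |

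**Illustration of the effect on the primary result.** These assumptions are not in the document, apart from 70%, which is the planned control rate. There is no true effect and healing is 70%. Second-of-pair patients differ in healing probability by g points between known HBOT slots and known control slots, always in favour of HBOT. A share s of those slots is steered. The bias in the risk difference is then 0.5 × s × g. Rejection is for a two-sided 5% test with 60 per arm, by simulation; with no steering it is about 5.2%.

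| Share steered | g | Bias (points) | Rejection |
|---|---|---|---|
| All | 10 | 5 | 9.4% |
| All | 20 | 10 | 22.7% |
| Half | 10 | 2.5 | 6.3% |
| Half | 20 | 5 | 9.5% |
| A quarter | 10 | 1.25 | 5.4% |
| A quarter | 20 | 2.5 | 6.2% |

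Hand check of the first row: the standard error is √(2 × 0.7 × 0.3 / 60) = 0.084 and 0.05 / 0.084 = 0.60. P(Z > 1.36) + P(Z < −2.56) is about 0.092, in line with 9.4%.

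**Power of an analysis in first-of-pair patients only** (about 30 per arm, 90% against 70%). The critical difference is 1.96 × √(2 × 0.8 × 0.2 / 30) = 0.202. The standard error under the alternative is √(0.30 / 30) = 0.10. Power = P(Z > (0.202 − 0.200) / 0.10) = P(Z > 0.02), about 49%.

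**The case against.** The strongest reply concerns timing. The article does not say that the second patient consents after the draw. If both members were enrolled and then drawn together, the pairing would give nothing away. This stands as a limit: 50% is the share under sequential entry, not an established fact about the trial. It does not remove the point, because the text neither requires nor implies joint enrolment and describes consent and randomisation as one step by the coordinator.

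Three further readings are tempting, and the document does not support them.
- A reader might infer that only the first member of each pair is randomised. That is wrong: one draw assigns both, and each has probability 1/2 of either arm. The weakness is predictability, not absence of chance.
- A reader might infer that the coordinator also decides who is eligible. The article does not say who judges eligibility. The overlap is explicit for consent and allocation only, and using the one-week interval to steer patients is an inference.
- A reader might take the 23% rejection rate as the expected error. It needs every second slot steered, always towards HBOT, with a 20-point gap. With a quarter steered, rejection is 5.4% to 6.2%.

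A manual draw is not in itself an error, so the absence of computer-generated numbers adds little. It is also fair to say that varying blocks do not restore 50% guessing in an unblinded trial.

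**Conclusion.** The point holds in this form: a fixed block of two, allocated by the person who takes consent, in an unblinded single-centre trial with no concealment step and no rule that both members consent before the draw. Followed as written, the plan allows up to 60 of 120 arms to be known before consent. The blinding it does provide cannot repair that.

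The counts of 50% and 75% rest on sequential entry. The bias of 5 to 10 points under full steering, or 2.5 to 5 points under half, also rests on the assumed prognostic gap. The upper end is half of the planned 20-point effect. Nothing in the document shows that steering took place; the defect is that the procedure leaves it possible. Because it touches the primary comparison and no planned analysis removes it, it should be corrected.

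**What to change.** **For remaining patients.** Replace the paired draw with a 1:1 list in randomly varying blocks that exclude size two (for example 4, 6 and 8), or with unrestricted randomisation. A team member without patient contact should prepare and hold the list. Each assignment should be revealed only after eligibility, consent and baseline are recorded. With blocks of 4, 6 and 8, guessing from past allocations still succeeds about 68% of the time, so predictability is reduced, not removed.

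**If the paired draw is kept.** Require both members to be consented and registered, with baseline recorded, before the draw. If this was already the practice, state it.

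**For patients already allocated.** Record enrolment order within the pair where it can be recovered, and compare baseline by arm among second-of-pair patients. Add a supportive sensitivity analysis in first-of-pair patients. With about 60 patients and about 50% power for 90% against 70%, it cannot replace the main analysis.

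**Cost.** A short amendment, preparation of the list, one extra sensitivity analysis, and two allocation schemes to report. N stays at 120. An unfinished last block of 8 can leave the arms at most 4 apart; unrestricted randomisation can leave a larger difference. Trial status gives recruitment from 4 July 2019 to a planned last entry on 31 August 2020, so the number of patients who can still benefit is not known from the document.
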